### Interventions

The intervention group will receive active tDCS as well as conventional rehabilitation, whereas the control group will receive sham tDCS as well as conventional rehabilitation. Conventional rehabilitation includes basic treatments and limb electrical stimulation. The treatment will be given six times a week for 4 weeks. To improve adherence, in terms of quality management, all procedures performed by the therapists involved in the study will be standardized, including our protocols, treatment methods, and evaluations.

#### Basic treatments

Controlling intracranial pressure, blood pressure, body temperature, and blood sugar of patients will be done as basic regular treatments. Other treatments include prevention and treatment of platelet aggregation, maintenance of electrolyte and acid-base balance, prevention of complications, inchoate rehabilitation treatment for patients, regular turning over for patients, attention to the placement of limbs, daily training of joint muscles, up and down stairs, and daily life self-care ability. Depending on the patient's situation, the clinician will manage each patient, including the drug use and prevention of complications.

#### Limb functional electrical stimulation

The Functional Electrical Stimulate (FES) equipment designed at Zhongshan Memorial Hospital of Sun Yat-sen University will be used in the study. The patient will receive four-channel stimulation, performed at a frequency of 30 Hz and a pulse width of 0.2 ms [9].

FES is the application of electrical stimulation to induce muscles that have lost nerve control to contract and produce movement. Its use will not affect the comparison of the effects of TDCS in this experiment and is one of the routine rehabilitation treatment projects for dysfunction after stroke.

#### Active tDCS

The intervention group participants will be treated with active tDCS. We will place the anode of the electrode in the dorsolateral prefrontal cortex (DLPFC) on the left side of the patients’ forehead, and cathode in the superior margin of the right orbit. The current intensity will be 1.5 mA according to the previous article [10]. The diameter of the electrode plate is 5cm. The unit type is MBM-I (Jiangxi Huaheng Jingxing Medical Technology Co., LTD, Nanchang City, Jiangxi Province, China). The treatment parameters will be 20 min per session, once a day, and 6 times a week. Patients will receive tDCS treatment alone, not at the same time as other treatments. The treatment will be carried out in the neuromodulation room, at the appointed time, by a specialized therapist.

#### Sham tDCS

Participants in the control group will be treated with sham tDCS treatment. The anode of the electrodes will be located at the DLPFC on the left side of the forehead and cathode at the superior margin of the right orbit. The current will only be input every 15 s during the initial phase, and there will be no current output during the intermediate 19.5 min of sham therapy. The rest of the parameters will be the same as for active stimulation.

### Trial outcomes

#### Outcome measures

In this study, primary outcomes will be measured at baseline and at the end of every week from the 1st to the 4th week. Secondary outcomes will be measured at baseline and the end of the 4th week. During each treatment, adverse events and untoward effects will be assessed. All outcome assessments will be independently performed by experienced and blinded assessors, the same one professional rehabilitation physician. A summary of all the measures in the trial is shown in Table 1.

**Table 1 Tab1:** Data on the design of the study

Point in time	Screening stage	Treatment period 1 (1 week)	Treatment period 2 (2 weeks)	Treatment period 3 (3 weeks)	Treatment period 4 (4 weeks)
Informed consent	**×**				
Inclusion and exclusion criteria	**×**				
Withdrawal, drop out, and termination criteria		**×**	**×**	**×**	**×**
Basic information	**×**				
Past medical history	**×**				
Therapeutic parameter record		**×**	**×**	**×**	**×**
**(*****Baseline*****) Fatigue Severity Scale (FSS)**	**×**	**×**	**×**	**×**	**×**
**Functional Assessment Chronic Illness Therapy (Fatigue) (FACIT-F)**	**×**				**×**
**Fatigue Impact Scale (FIS)**	**×**				**×**
**Specialized Quality of Life Scale in Stroke (SS-QOL)**	**×**				**×**
Overall efficacy evaluation					**×**
Complications	**×**	**×**	**×**	**×**	**×**
**Adverse events recorded**	**×**	**×**	**×**	**×**	**×**

#### Primary outcomes

##### Fatigue Severity Scale (FSS)

FSS is one of the most widely known and used scales composed of 9 items and evaluated by 7 points [11–15]. FSS points increase from 1 point (highly disagree) to 7 points (highly agree). In 1989, Krupp et al. developed the scale and applied it to patients with systemic lupus erythematosus and multiple sclerosis [16]. Aside from multiple sclerosis (MS), this scale has also been used in Parkinson’s disease, chronic fatigue syndrome, brain injury, and other diseases. The result will use the aggregate score as the patient’s score.

#### Secondary outcomes

##### Functional Assessment Chronic Illness Therapy (Fatigue) (FACIT-F)

The FACIT-F was developed in 1997 and first used to measure fatigue in oncology patients with anemia and is also a stand-alone questionnaire in the Functional Assessment in Cancer Therapy measurement system [17]. It has since been widened to include the assessment of chronic illnesses (as the FACIT measurement system). The current version of FACIT-F is the fourth. It has been used in assessing fatigue in patients with rheumatoid arthritis (RA), psoriatic arthritis (PsA), primary Sjögren’s syndrome (PSS), osteoarthritis (OA), and systemic lupus erythematosus (SLE) [18–27], as well as many other long-term conditions (e.g., multiple sclerosis, cancer, neurologic disorders).

##### Fatigue Impact Scale (FIS)

FIS is designed by Fisk to assess the impact of fatigue on quality of life. It is used to measure the impact of fatigue on patients’ physical, psychological, and cognitive functions in the first month.

##### Specialized Quality of Life Scale in Stroke (SS-QOL)

The purpose of this scale is to understand the current quality of life of stroke patients in our province and health defects after stroke. Through the analysis of the defect problem to determine the corresponding key rehabilitation content, it can help patients with stroke to maximize functional recovery and improve patient quality of life. The original SS-QOL questionnaire measures 12 domains with 49 items [28]. The domains and items were derived from interviews with stroke survivors in the USA. The validity of the SS-QOL scale has been examined in individuals after stroke in various countries, e.g., in Denmark with an ischemic stroke population [29], Nigeria (Yoruba language) [30], Mexico [31], and Germany, where a short and long version for survivors of hemorrhagic or ischemic stroke has been validated [32].

### Follow-up

After the 4-week treatment period, the patients will be followed up for 8 weeks. The medical staff will follow up with the participants by phone. Participants will be contacted every 2 weeks to record medication and rehabilitation. During the last week of follow-up (the 8th week after the intervention), participants will be referred for clinical evaluation to assess their prognosis and disability status.

### Study endpoints

The endpoints of the study are as follows:
In the event of a serious adverse reaction during the course of the test, the test will be terminated in time to protect the subject.In the event of a serious complication or deterioration in the course of the test, the test will be terminated.The test will be terminated if the subject is asked to withdraw from the clinical study.And if the patient does not cooperate and does not receive treatment and the therapist’s explanation is not working, then the study will be suspended.

The researchers will keep detailed records of why and when the subjects quit the study.

### Safety assessments

The medical staff will record adverse events (AEs) that occur at any time during treatment. If a serious AE occurs, the Ethics Committee of the First Affiliated Hospital of Nanchang University will determine if the participant needs to be withdrawn from the study. We will undertake to treat AEs free of charge.

### Sample size

The sample size calculation is based on improvement in scores on the Fatigue Severity Scale (FSS). According to similar published articles [33], the FSS scores after inventions are 20.66 ± 4.54 and 40.36 ± 9.58, *n* = 57. According to the study, treatment can probably improve the FSS by 19.7 points. Improvement will be measured according to the same sample size of the estimation formula:
$$ n=2\left[{\left(\upmu \alpha +\mu \beta \right)}^2{\sigma}^2\right]/{\delta}^2 $$

With a type I error of 5% (*α* = 0.05) and 90% power (*β* = 0.10), the estimated required sample size is 43 participants per group. Allowing for a 20% dropout rate during the study, a minimum total of 100 participants is needed to reach the target of 43 participants per group.

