### Trial design

The clinical study is a prospective, randomized controlled trial designed with double-blinded assessments. Since there is no clinically effective treatment, we will perform the superiority test. This study will be carried out with 100 hospitalized patients with PSF. All participants will be randomly allocated to either the intervention or control group in a 1:1 ratio. Each group will, therefore, be composed of 50 patients. Interventions in both parallel groups were identical except for effective tDCS treatment. The control group will receive conventional rehabilitation combined with sham tDCS treatment, whereas the intervention group will receive conventional rehabilitation combined with active tDCS treatment. This trial will be composed of a 4-week intervention and an 8-week follow-up period. From the first to the fourth week, the primary outcome Fatigue Severity Scale (FSS) will be measured at baseline on every weekend. The secondary outcomes Fatigue Impact Scale (FIS), Functional Assessment Chronic Illness Therapy (Fatigue) (FACIT-F), and Specialized Quality of Life Scale in Stroke (SS-QOL) will be performed at the end of the intervention period. Adverse events and untoward effects will be supervised in each treatment. The first affiliated Hospital of Nanchang University (NCU), which will undertake the study, is responsible for training rehabilitation therapists on the standard operating procedure and supervising the progress of this trial at all clinical sites. In addition, the randomization and blinding will be performed by an independent statistician from the Center of Evidence Based Medicine, NCU. A flow diagram of this trial is presented in Fig. 1.

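### The stated 43 per group does not follow from the protocol's own formula and inputs, which give about 4 to 5, so the effect behind 43 and its 90% power is not stated

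*Protocol article*

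**What the plan says.** The Sample size section of the protocol article takes its planning values from a published study: "the FSS scores after inventions are 20.66 ± 4.54 and 40.36 ± 9.58". From these it infers that "treatment can probably improve the FSS by 19.7 points". It then prints the usual formula for comparing two means, n = 2(u_α + u_β)²σ²/δ², sets α = 0.05 and β = 0.10, and reports that "the estimated required sample size is 43 participants per group". A 20% dropout allowance brings the total to 100.

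The section does not say which σ enters the formula or whether the test is one- or two-sided. The Trial design section says only that "we will perform the superiority test", with patients "randomly allocated to either the intervention or control group in a 1:1 ratio". The article states no other FSS difference, SD or minimum important difference.

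**The concern.** Everything the formula needs is printed next to the result except the choice of σ and the sidedness, and neither choice can plausibly move the answer from single figures to 43. The quoted difference is more than two SDs, and an effect that large needs only a handful of patients per group.

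What is at stake is the meaning of the power statement. As written, the trial has 90% power for a 19.7-point difference. If 43 came from other inputs, the trial was sized for a different and much smaller effect that the reader is not told. An ethics committee, the monitoring committee or a later reader then cannot tell what difference the trial was designed to detect, or why 100 patients are needed when the stated inputs call for about 10.

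**Working it through.** **Inputs**, all from Sample size unless noted:
- δ = 40.36 − 20.66 = 19.7 FSS points
- SDs 4.54 and 9.58; average-variance SD = √[(4.54² + 9.58²)/2] = √56.19 = 7.50
- α = 0.05 and power 90%; sidedness not stated, so both are tried
- 1:1 allocation (Trial design)

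**Attempt to reproduce 43.** For a two-sided test, 2(1.960 + 1.282)² = 21.01, and δ² = 388.09. Hence n per group = 21.01 × σ²/388.09. For a one-sided test, 2(1.645 + 1.282)² = 17.13 replaces 21.01.

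| σ | two-sided, raw | rounded up | exact t | one-sided, raw |
|---|---|---|---|---|
| 4.54 | 1.12 | 2 | 3 | 0.91 |
| 7.50 | 3.04 | 4 | 5 | 2.48 |
| 9.58 | 4.97 | 5 | 7 | 4.05 |
| 14.12 (the two SDs added) | 10.80 | 11 | 12 | 8.80 |

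The last row is not a legitimate choice of σ. It is there to show that even an extreme misuse of the SDs stops at 11 or 12. Other slips were also tried: splitting α over four or five looks, leaving σ or δ unsquared, and reading the SDs as standard errors. None came within 2 patients of 43.

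**Size of the gap.** 43/5 = 8.6 and 43/4 = 10.75, so the stated figure is about 9 to 11 times the derived one.

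**σ needed for 43 with δ = 19.7.**
- Two-sided: √(43 × 388.09/21.01) = 28.2
- One-sided: √(43 × 388.09/17.13) = 31.2
- Against the quoted SDs: 28.2/9.58 = 2.9 times the larger one, and 28.2/7.50 = 3.8 times the average-variance one

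**Power at 43 for 19.7 points.** The standardised effect is 19.7/9.58 = 2.06 to 19.7/7.50 = 2.63. Power is practically 100%.

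**What the numbers can detect** (two-sided 5% test and 90% power, both assumed for this step). The standardised difference is √(21.01/n).
- n = 43: √(21.01/43) = 0.70 (0.71 by exact t). In points: 0.699 × 7.50 = 5.2 and 0.699 × 9.58 = 6.7.
- n = 40, which is 50 per group less 20%: √(21.01/40) = 0.725 (0.73 by exact t). In points: 0.725 × 7.50 = 5.4 and 0.725 × 9.58 = 6.9.

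**The case against.** Three points on the other side deserve weight.

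First, the error is in the safe direction. Against the only effect that the protocol names, 43 per group is far more than enough, and a null result would be read from its confidence interval rather than from the planning difference. This stands. A reader might infer from a failed sample-size check that the trial is underpowered, but the stated figures do not support that. The harm is a justification that cannot be reproduced and a target effect that is not disclosed.

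Second, a reader might go further and say that 43 is impossible for any SD. The FSS is "composed of 9 items and evaluated by 7 points" and the aggregate score is used, so a single score runs from 9 to 63 and its SD cannot exceed 27, which is below 28.2. The protocol does not allow that conclusion, because the section says that the calculation rests on improvement in scores, which can mean a change score. A change on this scale can run from −54 to +54, so its SD is bounded by 54. With entry limited to a mean FSS above 4 (a total above 36), the change still spans about 81 points and the bound is about 40. An SD of 28 is implausible and far from the quoted values, but it is not excluded.

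Third, the protocol does name an effect, 19.7 points. It would be wrong to say that no effect is given. What is missing is the effect that produces 43. The cited study is not available here, so a misquoted input cannot be told apart from a miscalculation.

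**Conclusion.** The mismatch stands. The protocol's formula with its own difference, SDs, α and power gives about 4 to 5 per group (5 to 7 by exact t), and the article gives no other difference or SD that would lead to 43. The conclusion does not depend on sidedness, since a one-sided test needs fewer patients still.

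The trial is over-sized for the effect that it quotes, the 90% power statement does not describe the design, and the inputs behind 43 are unknown. The figure of 0.70 SD is worked backwards from 43 under an assumed two-sided 5% test. A reader might take it for the planned target, but nothing in the document shows that it was, and no clinical rationale for 5 to 7 points is given. This should be corrected before the sample size is relied on; it is not a reason to change the number enrolled.

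**What to change.** Keep enrolment at 100 and rewrite the paragraph.

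1. State the δ, σ and sidedness actually used, so that a reader can reproduce the result with the printed formula. Check the quoted planning values against the cited study while doing so.
2. Remove the derivation of 43 from a 19.7-point difference.
3. If the inputs cannot be recovered, say so and give the detectable difference openly as a back-calculation, at the number expected after dropout. For example: assuming a two-sided 5% test, 40 evaluable patients per group (50 less 20%) give 90% power for a standardised difference of about 0.72 to 0.73, which is about 5.4 to 6.9 FSS points for an SD of 7.5 to 9.6. The values at 43 per group (about 0.70; 5.2 to 6.7 points) can stand beside it. The 40 belongs in the text because 100 enrolled with 20% dropout does not leave 43 per group.

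The cost is one paragraph. Design and recruitment do not change. The trial would then quote a much smaller detectable effect than 19.7 points, and the sponsor would have to say whether a difference of that size matters to patients.

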### Recruitment

We will publish our recruitment and current results on the website of the First Affiliated Hospital of Nanchang University from January 1, 2020 to December 31, 2025. Our team will search the patient's medical records through the computer patient record system. We will select patients who are eligible for inclusion and inform the patient and his/her family of the information about the trial by phone or email. Interested families will be encouraged to contact the project manager for more information.

### Randomization and allocation concealment

In this study, randomization and allocation of hidden blocks will be used. Participants will be assigned to either the intervention or control group in a ratio of 1:1. The order of randomization will be derived using the statistical software SPSS24.0 IBM and performed by an independent statistician from the evidence-based Medicine Center NCU who will not participate in the trial. In addition, randomly assigned ratings will be hidden from the results assessors and statistical analysts. After assessing the basic information of the participants, the allocation of the eligible participants will also be concealed from their caregivers and therapists, including acupuncturists and cognitive therapists, who will be assisting patients to receive treatment.

### Blinding

Because of the double-blind implementation of this study, the “third-party” personnel who did not participate in the experiment will manage and supervise the implementation of the blind method:
Patients will not be allowed to open the envelopes indicating the order in which they will be involved in the study. The tDCS model is assumed to be modes A and B, and the project implementer will not know what the stimulus represents.A mode is the active stimulus, and B is the sham stimulus; treatment outcomes will be assessed by third-party assessors who will not be aware of the grouping.In order to prevent the analyst’s subjective tendency in the process of data analysis, the first non-blind method will be performed before the statistical analysis is completed. In other words, the analyst will know that patients are divided into two groups, but will not know which group is the intervention group. After statistical analysis, a second non-blind test will be performed to determine which group will be the intervention group.

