## Discussion

As a new method of brain function research and treatment, tDCS has the advantage of being a painless, noninvasive, simple operation with a curative effect. As a non-invasive brain stimulation technology, tDCS can stimulate or inhibit the cerebral cortex and promote plasticity and functional reorganization of the functional areas of the cerebral cortex to encourage rehabilitation in stroke [34, 35]. Some studies show that it can help with fatigue [36]. In terms of fatigue symptoms, the stimulation sites of tDCS in clinical research include the bilateral M1 area, bilateral S1 area, and left DLPFC. Ferrucci et al. studied 23 MS patients with bilateral M1 area anode electrical stimulation, Tecchio et al. treated 10 MS patients with S1 area electrical stimulation, and the patients’ fatigue was reduced [37]. Chalah et al. compared the effects of the left DLPFC and right posterior parietal cortex (PPC) on MS fatigue. The results showed that left DLPFC improved fatigue symptoms, while right PPC reduced emotional scores. In order to ensure the authenticity of the test results, a double-blind test design will be adopted. Fatigue Severity Scale (FSS), Fatigue Impact Scale (FIS), Functional Assessment Chronic Illness Therapy (Fatigue) (FACIT-F), and Specialized Quality of Life Scale in Stroke (SS-QOL) will be used as evaluation indices to evaluate the changes of patients’ fatigue. The aim of this project is to investigate the effect of tDCS on post-stroke fatigue and find new interventions to improve PSF.

The related scale used to evaluate the fatigue degree of patients is greatly affected by the subjective factors of patients. Therefore, the experimental results are easily affected by various factors, such as the favorite degree of therapists. However, the FSS has good internal consistency, reliability, construct, and criterion validity and is sensitive to change. It has been evaluated in several conditions where it is the recommended fatigue scale [38, 39]. Thus, we can maximize the accuracy of the experiment.

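### The protocol prints the key to its own two-letter device code (A active, B sham), so the blinding of whoever delivers tDCS is not protected as written

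*Protocol article*

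**What the plan says.** The Blinding section puts people from outside the trial in charge of the blind. It describes the device code as follows: "The tDCS model is assumed to be modes A and B, and the project implementer will not know what the stimulus represents". The sentence directly after it gives the meaning of the code: "A mode is the active stimulus, and B is the sham stimulus". The same sentence goes on to say that third-party assessors, unaware of grouping, will rate outcomes.

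The section on randomization and allocation concealment extends the promise to treating staff: "the allocation of the eligible participants will also be concealed from their caregivers and therapists". According to the Active tDCS section, treatment takes place in the neuromodulation room, "at the appointed time, by a specialized therapist".

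No further coding layer is described. The article mentions no participant-specific codes, no multiple codes per arm, and no key withheld from trial documents.

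**The concern.** A mode letter blinds its user only while its meaning is secret. Here the promise of secrecy and the meaning stand in consecutive sentences of the same document. Anyone who sees the letter and has read that paragraph knows the arm.

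A second weakness remains even without the printed key. Because each letter has one meaning for the whole trial, learning the arm of a single participant, for example through an emergency unblinding, decodes all the others.

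What is at stake is the primary outcome. The FSS is a self-report scale, and the Discussion accepts that such scales depend heavily on subjective factors in the patient. It adds that "the experimental results are easily affected by various factors, such as the favorite degree of therapists". An operator who knows the arm could, even unintentionally, convey more or less expectation of benefit. A blinded assessor cannot remove an effect that has already entered the patient's own answers.

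**Working it through.** The plan gives no figure on this point, so there is nothing to reproduce. The check sets the statements side by side and then counts.

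**Inputs**
- Code: two labels (Blinding).
- Key: A is active and B is sham (Blinding).
- Claimed blind: the implementer (Blinding) and the therapists (Randomization and allocation concealment).
- Delivery: a specialized therapist (Active tDCS). The Sham tDCS section keeps the other parameters the same.
- Participants: 100, allocated 1:1, so 50 per arm (Trial design).
- Sessions: six per week for 4 weeks (Interventions), so 6 × 4 = up to 24 per participant.

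**Step 1: consistency.** "the project implementer will not know what the stimulus represents" can hold only if the implementer either never sees the letter or never learns the key. The article secures neither. It does not say who sets the mode or what the device displays, and it publishes the key.

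**Step 2: what the operator could know.**

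| Sees the letter | Knows the key | Allocations identifiable |
|---|---|---|
| No | Either | None from the letter |
| Yes | No | None directly, but patients fall into two visible groups |
| Yes | Yes | 50 on A + 50 on B = 100 of 100 |

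**Step 3: one disclosure, with the key kept secret.** Under a single A/B pair, learning one participant's arm fixes the meaning of that letter, and of the other by elimination. The remaining 100 − 1 = 99 allocations follow for anyone who sees the letters.

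**Step 4: alternatives.** With k codes per arm in equal use (k of 2 or more), one disclosure decodes the participants who share that code, which is 50/k of them. As an illustration only, k = 5 gives 50/5 = 10 participants. With a separate code for each participant, one disclosure decodes 1. Re-drawing a single A/B pair removes the printed key but leaves the figure in Step 3 at 99.

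**Step 5: size of bias.** The documents give no estimate of how far an informed operator would move FSS scores, so no bias figure can be computed.

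**The case against.** The strongest reply is that the letters may be placeholders. "The tDCS model is assumed to be modes A and B" can be read as naming the modes for the reader and not as describing the device display. The Data sharing section refers to a separate full protocol, where code handling could be set out, and third-party personnel are said to control the blind. No sentence says that the treating therapist selects or sees the mode. These points stand. They limit the conclusion to a conditional one and lower confidence. They do not remove the contradiction, because the article itself publishes a key for the only code it describes.

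Other safeguards also stand. Assessors and data collectors are described as blinded, and the letters do not directly expose patients. The Discussion's remark about therapists is ambiguous: it may refer to how much patients like their therapist and not to knowledge of allocation. It supports the sensitivity of the outcome only loosely.

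A reader might infer more than the text supports:
- **Staff are taught the key.** The Trial design section says the hospital "is responsible for training rehabilitation therapists on the standard operating procedure". It does not say that this procedure contains the key or that operators receive the protocol.
- **Upcoming allocations become predictable within blocks.** Block size is not given, the sequence comes from an independent statistician, and neurologists do the screening. Nothing links the tDCS operator to enrolment.
- **Co-treatment is biased.** tDCS is given separately from other treatments, and the clinician manages medication. The documents do not put co-treatment in the operator's hands.
- **Analyst blinding is void.** That would require the analysis dataset to carry the device letters, which is stated nowhere. The Blinding section says the analyst will not know which group is which.

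**Conclusion.** The point holds in a limited form. The protocol promises that the implementer and the therapists do not know the allocation, then prints the key to a single trial-wide code. Operator blinding is therefore not protected as written.

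If the delivering therapist sees the printed letters and knows the key, all 100 allocations are identifiable. If the therapist sees the letters and the key had stayed secret, one disclosure would still reveal the other 99. Both statements assume that the letters are the live device labels and that the operator sees them; the article states neither.

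It would go too far to conclude that blinding has been broken or that the trial is not double-blind. Assessor blinding is described separately, and the effect on FSS cannot be quantified. The matter should be fixed, with moderate confidence: the contradiction is plain on the page, while its practical reach depends on details the article does not give.

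**What to change.** 1. Remove the sentence giving the key from the protocol. Deletion alone is not enough, because the meaning of A and B has already been disclosed.
2. Have the independent statistician re-draw the device labels, preferably as participant-specific codes or several codes per arm. If the device allows only two labels, re-draw their meaning and keep it out of every trial document, accepting that one disclosure would still decode the whole trial.
3. Let only the third party hold the key, with a sealed emergency copy for each participant so that one unblinding does not expose the rest.
4. As a precaution, give the analyst group labels unrelated to the device labels.
5. State who sets the mode and what that person sees, which would settle the inference on which this point depends.

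The cost is a code list, re-labelling, amended wording and slightly more administration at each session. The statistician and the third-party personnel are already in place. No treatment parameter changes.
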